### Outcome measures

At baseline, demographic and clinical characteristics will be collected for all participants, including age, sex, educational level, occupation, and disease duration. In addition, the types and spatial distribution of pathological response points in the temporal and occipital regions will be documented.

### Primary outcome measures

The primary clinical outcome will be activities of daily living, assessed by the Barthel Index (BI).

Activities of daily living: Activities of daily living will be assessed using the BI (36), which is widely used to evaluate basic activities of daily living and functional recovery before and after treatment. The total score ranges from 0 to 100, with higher scores indicating greater functional independence and lower levels of dependence.

### Secondary outcome measures

Secondary outcome measures will include the National Institutes of Health Stroke Scale (NIHSS) and the modified Rankin Scale (mRS).

National Institutes of Health Stroke Scale (NIHSS): The NIHSS (37) is a brief, convenient, and reliable scale for assessing neurological deficits in patients with stroke. It will be used to evaluate the severity of neurological impairment and changes in neurological status over the course of the intervention.

Modified Rankin Scale (mRS): The mRS (38) is a 7-point scale (0–6) used to assess the degree of functional disability and global outcome after stroke. It primarily reflects the level of functional independence, including bodily function, mobility, and participation in activities of daily living.

### Secondary and exploratory neuroimaging outcomes

The neuroimaging outcomes will be assessed in the predefined imaging subgroup and will include indices derived from rs-fMRI and DTI analyses. rs-fMRI measures will focus primarily on resting-state functional connectivity (FC), particularly resting-state network alterations evaluated using independent component analysis (ICA). DTI measures will focus primarily on fractional anisotropy (FA), with particular attention to the corticospinal tract (CST) and other major motor-related white matter pathways. Mean diffusivity (MD) will be examined as an exploratory diffusion metric.

### Functional MRI and DTI data acquisition

All MRI data will be acquired on a 3.0 T Magnetom Prisma scanner (Siemens, Erlangen, Germany) at The Second Affiliated Hospital of Guangzhou University of Chinese Medicine (Guangzhou). Before scanning, all participants will be screened for MRI contraindications and prepared according to standard safety procedures. During image acquisition, participants will lie in the supine position, be instructed to close their eyes, relax, remain awake, and minimize head movement. Ear protection and foam padding will be used, and participants will be monitored throughout the examination to ensure safety and compliance.

A set of localizer images will first be obtained to confirm head position and slice orientation (53 slices; repetition time (TR) = 520 ms; echo time (TE) = 4.92 ms; slice thickness = 2.0 mm; field of view (FOV) = 192 × 192 mm^2^; flip angle = 60°; voxel size = 3.0 × 3.0 × 2.0 mm^3^; matrix = 256 × 256).

For structural imaging, three-dimensional T1-weighted images of the whole brain will be acquired using a gradient-echo sequence. The scan parameters will be: 192 slices; TR = 1900 ms; TE = 2.26 ms; slice thickness = 1.0 mm; FOV = 256 × 256 mm^2^; flip angle = 9°; voxel size = 1.0 × 1.0 × 1.0 mm^3^; matrix = 256 × 256.

Resting-state functional images will be collected using a T2-weighted gradient-echo echo-planar imaging (EPI) sequence for BOLD fMRI. The protocol will include 37 axial slices with TR = 2000 ms, TE = 30 ms, slice thickness = 3.0 mm, FOV = 224 × 224 mm^2^, flip angle = 90°, voxel size = 3.5 × 3.5 × 3.0 mm^3^, and a matrix of 64 × 64.

For DTI, diffusion-weighted images will be obtained with 25 slices (TR = 3,500 ms; TE = 95 ms; slice thickness = 4.0 mm; FOV = 220 × 220 mm^2^; voxel size = 1.7 × 1.7 × 4.0 mm^3^; matrix = 128 × 128).

### Patient safety

Safety will be assessed throughout the intervention period. All acupuncture procedures will be performed in strict accordance with standardized acupuncture operation guidelines to minimize the risk of adverse events. If any acupuncture-related adverse reactions occur during treatment—such as needle stagnation, vasovagal syncope (needle fainting), or subcutaneous hematoma—appropriate management will be provided immediately, the event will be graded, and detailed records will be kept. No formal data monitoring committee is planned because this is a single-center, low-risk acupuncture trial; safety will be monitored by the investigators and the ethics committee.

Adverse events will be graded as follows:

Grade 1: Safe, no obvious discomfort.Grade 2: Mild adverse reactions, such as transient burning, itching, or pain at the acupoint after needling, which resolve spontaneously without intervention.Grade 3: Moderate adverse reactions that require medical management, after which the patient can continue the treatment protocol.Grade 4: Severe adverse reactions that prevent continuation of treatment and require termination of the trial for that patient.

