**Figure 1 fig1:**
[figure not shown]
Flowchart of the randomized controlled trial. BI, Barthel Index; NIHSS, National Institutes of Health Stroke Scale; mRS, modified Rankin Scale; fMRI, functional magnetic resonance imaging; DTI, diffusion tensor imaging.

**Table 1 tab1:** Schedule of enrolment, interventions, and assessments.

	Study period				
	Screening/Enrolment	Baseline (Day 0)	Treatment period (Day 1–14)	Post-treatment (Day 14)	Follow-up (1 month post-treatment)
Eligibility assessment	**×**				
Informed consent	**×**				
Brain MRI confirmation of brainstem infarction	**×**				
Demographic and clinical characteristics		**×**			
Documentation of pathological response points		**×**	**×**		
Randomization		**×**			
Standard medical management			**×**		
Routine rehabilitation			**×**		
Conventional acupuncture (both groups)			**×**		
Shallow Acupuncture (adjunctive Shallow Acupuncture group)			**×**		
BI		**×**		**×**	**×**
NIHSS		**×**		**×**	**×**
mRS		**×**		**×**	**×**
fMRI and DTI (imaging subgroup only)		**×**		**×**	
Adverse event/safety monitoring			**×**	**×**	

BI, Barthel Index; NIHSS, National Institutes of Health Stroke Scale; mRS, modified Rankin Scale; fMRI, functional magnetic resonance imaging; DTI, diffusion tensor imaging.

The study protocol has been reviewed and approved by the Ethics Committee of Guangdong Provincial Hospital of Chinese Medicine (Ethics Reference No: YE2024-202-01, YE2024-203-01). The trial has also been registered in the International Traditional Chinese Medicine Clinical Trial Registry (ITMCTR; registration number: ITMCTR2024000456).

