### Clinical data analysis

All clinical statistical analyses will be performed by independent statisticians who are blinded to group allocation, using SPSS version 26.0 (IBM Corp., Armonk, NY, USA). The primary clinical analysis will focus on the between-group difference in BI change after treatment. Analyses of clinical outcomes will primarily follow the intention-to-treat principle, including all randomized participants according to their allocated group. A per-protocol analysis may also be conducted as a sensitivity analysis in participants who complete the assigned intervention. Missing data will be handled using appropriate statistical methods depending on the extent and pattern of missingness.

Continuous variables will be presented as mean ± standard deviation (SD) when normally distributed or as median with interquartile range (IQR) when non-normally distributed. Categorical variables will be summarized as frequencies and percentages. Between-group comparisons of continuous variables will be performed using the independent-samples t-test for normally distributed data or the Mann–Whitney U test otherwise. Within-group changes over time will be assessed using paired-samples t-tests or Wilcoxon signed-rank tests, as appropriate. For categorical or ordinal variables, the chi-square test, Fisher’s exact test, or rank-sum test will be used as appropriate. Clinically relevant concomitant medications and rehabilitation interventions will be summarized by group using descriptive statistics, with attention to the magnitude and clinical relevance of any between-group differences. If clinically meaningful imbalances in co-interventions are observed, these factors will be considered in the interpretation of the results, and exploratory sensitivity analyses or covariate-adjusted analyses may be performed as appropriate.

For repeated clinical assessments, changes over time and between-group differences will be further evaluated using repeated-measures analysis or an equivalent mixed-effects approach, where appropriate. The relationships between clinical outcome measures and imaging parameters will be assessed using Pearson or Spearman correlation analyses, depending on the distribution of the data. All statistical tests will be two-sided, and a *p*-value < 0.05 will be considered statistically significant.

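### Adverse-event monitoring is scheduled only to Day 14 although patients are assessed again at 1 month, and the only explicit recording rule covers acupuncture-related reactions, which does not match the wider wording in Table 1 and the grading scale

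*Protocol article*

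**What the plan says.** **Window.** Patient safety states: "Safety will be assessed throughout the intervention period". In Table 1 the row "Adverse event/safety monitoring" is marked for the treatment period (Day 1–14) and for the post-treatment visit (Day 14). The cell for the follow-up visit 1 month after treatment is empty. The rows for the Barthel Index (BI), NIHSS and mRS are marked at that visit.

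**Trigger for recording.** The one sentence in Patient safety that says events will be graded and recorded begins "If any acupuncture-related adverse reactions occur during treatment". Its examples are needle stagnation, needle fainting and subcutaneous hematoma.

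**Scale.** The grading list is introduced by "Adverse events will be graded as follows". It starts with "Grade 1: Safe, no obvious discomfort". Grade 2 reads "Mild adverse reactions, such as transient burning, itching, or pain at the acupoint after needling", and Grades 3 and 4 are also worded as reactions.

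**Setting.** Blinding says that participants and acupuncturists cannot be blinded, while outcome assessors are. Patient safety says that no data monitoring committee is planned and that the investigators and the ethics committee monitor safety.

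**The concern.** Two separate features of the plan reduce what can be learned about harm.

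The first is timing. The patients come back at 1 month and three scales are completed, but no safety enquiry is scheduled. An event that occurs or becomes apparent after Day 14 is collected only if somebody happens to report it.

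The second is attribution. If the narrow sentence is the operating rule, an event enters the record only after someone has judged it related to acupuncture. In an open-label add-on trial that judgement can differ between arms, because one arm receives an extra needling procedure. Interventions also describes guided functional exercises while the shallow needles are retained, and describes them only for the experimental arm. Eligible patients may have vertigo, balance impairment or ataxia. A fall during such an exercise is a plausible event that one person might call acupuncture-related and another might not.

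At stake is the quality of the safety information, since no analysis can recover events that were never collected.

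**Working it through.** The protocol gives no figure for safety to reproduce, and the sample size does not bear on this point. The check is a comparison of the relevant places, plus one ratio.

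**1. Do text and table agree on the window?** Yes. Patient safety limits assessment to the intervention period. Table 1 marks Day 1–14 and Day 14 and leaves the 1-month cell empty. Two places give the same window, so it reads as a stated choice and not as detail lost in condensing the protocol.

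**2. What does the window leave out?** Treatment is given once daily for 14 consecutive days (Interventions, Tables 2 and 3), so the last session and the last scheduled safety check both fall on Day 14. With one month taken as 30 days (an assumption; the document gives no day count):

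- participation from first session to last visit = 14 + 30 = 44 days
- share with scheduled safety monitoring = 14 / 44 = 0.318, about 32%
- days without it = 30, about 68%

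This is calendar time only. All treatment days are covered, so 68% is not a share of treatment-related risk. A reaction to the Day 14 session that shows itself after the Day 14 check is outside the window.

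**3. Do the places agree on which events count?**

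| Place | Term used | Limited by cause? |
|---|---|---|
| Table 1 row | adverse event | no |
| Introduction to the grading scale | adverse events | no |
| Sentence on grading and recording | acupuncture-related adverse reactions | yes |
| Grades 2–4 | adverse reactions | by wording, yes |

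The wide and the narrow terms stand side by side, and only the narrow one is attached to an instruction to record. A site following the instruction literally could leave out unrelated events. A site following Table 1 could include them.

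**4. Do other data fill the gap?** In part. NIHSS and mRS (range 0–6) at 1 month in both arms would show serious neurological worsening, but as a score without a cause or a date. Conventional acupuncture group says that blinded assessors record concomitant medications and rehabilitation in both groups throughout the study period, so a treatment change could hint at an event. Neither is a record of adverse events.

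**5. What does Grade 1 mean?** It describes a patient with no event, on a scale introduced as grading adverse events. Incidence is therefore clear only if it is stated to be counted from Grades 2–4.

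**The case against.** The strongest reply is that the article does not say what a critical reader may infer from it. Four stronger readings are tempting, and the document supports none of them.

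- **That late or unrelated events are never compared between arms.** Clinical data analysis offers general tests ("For categorical or ordinal variables, the chi-square test, Fisher’s exact test, or rank-sum test will be used as appropriate") and excludes nothing. A safety analysis may stand in the full protocol or the analysis plan, which are not shown.
- **That recurrent stroke, falls or readmission are not recorded.** The narrow sentence says how acupuncture-related reactions are handled; it does not say that other events are ignored. Uncertain recording is as far as the text goes.
- **That unblinded staff decide what is counted.** The document does not say who assesses relatedness, and Blinding limits the acupuncturists to delivering treatment.
- **That incidence would be 100% in both arms because every event-free patient is Grade 1.** Nobody proposes that tabulation. The scale can be read as an ordinal rating with a no-event level, and the label does not cause any data to be missing.

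It would also be wrong to support the point with the upper bound on an event rate when no events are seen. With 31 per arm that bound is 1 − 0.05^(1/31) = 9.2%, but it depends only on the number of patients. It is the same for 14 days as for 44.

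Further, the reactions that the protocol names mostly arise at or soon after needling, safety is not a listed outcome, and the absence of a monitoring committee is disclosed with a reason.

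All of this stands, and it confines the point to a short window, inconsistent wording and an awkward label. It does not remove the empty cell at a visit that takes place anyway, nor the conflict between the two terms.

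**Conclusion.** The point holds in a limited form. Scheduled adverse-event monitoring ends on Day 14 while efficacy assessment continues to 1 month. The only explicit recording rule is narrower than the wording of Table 1 and of the scale's introduction. It follows that events after Day 14 have no scheduled collection, and that recording of events not attributed to acupuncture is uncertain. The size is 14 of about 44 days under the 30-day assumption; no event rate or bias can be computed from the document. The Grade 1 label is a separate and minor wording matter.

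The conclusion assumes that the article reports the full protocol's safety window and recording rule faithfully. If the full protocol already records all events to 1 month, only the article's text and Table 1 need correcting. Neither the primary BI comparison nor the sample size is touched. I class this as a cheap improvement.

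**What to change.** 1. In Patient safety, state that all adverse events are recorded in both arms regardless of attributed cause, from the first session through the existing 1-month visit, with serious events listed separately. Relatedness can then be recorded as an attribute of each event instead of a condition for recording it.
2. In Table 1, add a mark for adverse-event monitoring in the 1-month follow-up column.
3. Use one term consistently in the recording sentence, the scale and Table 1.
4. Label Grade 1 as no event and say that incidence is counted from Grades 2–4.

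The cost is a few extra questions at a visit already scheduled, slightly more data handling, and small edits to the text and one table. No added visit or patient is needed, and the primary analysis does not change.

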**Methods and analysis:**

This is a single-center, randomized, assessor- and statistician-blinded, pragmatic add-on controlled trial. A total of 62 patients with brainstem infarction will be randomly assigned in a 1:1 ratio to a conventional acupuncture group or an adjunctive Shallow Acupuncture group. In keeping with routine inpatient practice in the acupuncture department, both groups will receive standard medical management, routine rehabilitation, and conventional acupuncture, while the adjunctive Shallow Acupuncture group will additionally receive Shallow Acupuncture once daily for 14 consecutive days. The primary clinical outcome will be activities of daily living, assessed by the Barthel Index. Secondary clinical outcomes will include the National Institutes of Health Stroke Scale and the modified Rankin Scale. Exploratory indicators will include measures derived from rs-fMRI and DTI. rs-fMRI analyses will focus primarily on resting-state functional connectivity, whereas DTI analyses will focus primarily on fractional anisotropy; mean diffusivity will be examined as an exploratory diffusion metric. Clinical outcomes will be assessed at baseline, post-treatment, and 1-month follow-up, and neuroimaging assessments will be performed at baseline and post-treatment.

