### Withdrawal criteria

Subjects will be withdrawn from the study if any of the following occur:

Enrollment despite not meeting the predefined inclusion criteria (mis-enrollment).Failure to receive the assigned intervention as per protocol, or failure to complete study documentation in a way that materially affects outcome assessment.Poor treatment adherence or voluntary withdrawal from the study during the intervention period.Initiation, addition, or modification of other treatments during the trial that may interfere with the evaluation of study outcomes.

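### The Grade 4 adverse-event rule ends the trial, not only the needling, for a patient with a severe reaction, and so loses outcomes the intention-to-treat analysis needs

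*Protocol article*

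**What the plan says.** The Patient safety section of the protocol article ends with a four-level grading of adverse events. Grade 4 reads "Severe adverse reactions that prevent continuation of treatment and require termination of the trial for that patient". Grade 3, just above it, reads "Moderate adverse reactions that require medical management, after which the patient can continue the treatment protocol". The same section says that reactions will be managed, graded and recorded in detail.

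The Withdrawal criteria section lists reasons for which a patient leaves the study, as opposed to the treatment. One of them is "Failure to receive the assigned intervention as per protocol". Adverse reactions have no entry of their own there.

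On the analysis side, Clinical data analysis states: "Analyses of clinical outcomes will primarily follow the intention-to-treat principle, including all randomized participants according to their allocated group". It also states: "The primary clinical analysis will focus on the between-group difference in BI change after treatment". Missing data are left to suitable methods chosen according to how much is missing and in what pattern. Table 1 schedules BI, NIHSS and mRS at baseline, Day 14 and 1 month after treatment, with no exception for patients who stop needling.

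**The concern.** Stopping a treatment and leaving a trial are separate decisions. An intention-to-treat analysis depends on keeping them apart, because it needs the outcomes of patients who stopped treatment. The Grade 4 wording merges them. A patient whose needling stops on, say, Day 5 would have baseline scores only, and therefore no BI change for the primary analysis.

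The reason for the loss is a reaction to the treatment, so the missing values cannot be assumed unrelated to treatment. Needle exposure also differs between arms by design. The fixed conventional prescription amounts to 15 needles per session (counting bilateral points twice), and the adjunctive arm adds roughly 15 to 20 more. The article gives no reaction rate by arm, so whether losses would actually be unbalanced is not known.

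At stake are the primary BI comparison and both secondary scales. Values that an already scheduled visit could have measured would have to be replaced by a statistical model.

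**Working it through.** **1. What the wording requires.** Grade 4 carries two consequences: treatment cannot continue, and the trial is terminated for that patient. If the second meant only that needling stops, it would repeat the first. Grade 3 speaks of the treatment protocol, so the scale itself distinguishes treatment from trial. Nothing in the article says that a patient who stops needling is still assessed. The second withdrawal criterion points the same way, because a patient who misses the remaining sessions after a Grade 4 reaction has not received the intervention as assigned. The article does not suggest that recording of the event itself would stop.

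**2. What is lost per patient.** Table 1 has 3 scales (BI, NIHSS, mRS) at 2 post-baseline visits (Day 14, 1 month): 3 × 2 = 6 scores if the reaction precedes the Day 14 assessment. One patient is 1/31 = 3.2% of an arm.

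**3. The plan's own sample size.** Inputs from Sample size calculation: difference 4.84 (17.50 − 12.66), SD 5.22, two-sided alpha 0.05, power 90%, dropout 15%.
- Normal-approximation formula: 2 × (1.960 + 1.282)² × 5.22² / 4.84² ≈ 24.4, rounded up to 25 per group.
- Exact two-sample t-test: 25.44, rounded up to 26 per group, as stated.
- Dropout: 26 / 0.85 = 30.6, rounded up to 31 per group, 62 in total, as stated.

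**4. Power under loss (t-test).**

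| Patients analysed | Power |
|---|---|
| 31 vs 31 | 94.9% |
| 31 vs 30 | 94.5% |
| 31 vs 28 | 93.8% |
| 26 vs 26 | 90.6% |

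The allowance of 31 − 26 = 5 per arm absorbs a few losses, so power is not the problem.

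**5. Possible shift in an arm mean.** Let k of 31 patients be lost, and let their mean BI change differ by D from the mean m of those retained. The full-arm mean is [(31 − k)m + k(m − D)] / 31 = m − kD/31, while the observed mean is m. The shift is therefore kD/31. The article gives neither k nor D. I take D from 5.22 (one planning SD) to 17.5 (the whole planned gain in the adjunctive arm).

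| k | D = 5.22 | D = 17.5 | Share of 4.84 |
|---|---|---|---|
| 0 | 0 | 0 | 0 |
| 1 | 5.22/31 = 0.17 | 17.5/31 = 0.56 | 3.5% to 11.7% |
| 2 | 10.44/31 = 0.34 | 35/31 = 1.13 | 7.0% to 23.3% |

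The sign of D is unknown, so these are sizes and not directions.

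**The case against.** The strongest reply is that the line is a severity definition and not a follow-up rule. It names no visit or scale, and ending the trial for a patient might loosely mean ending trial treatment. A condensed article can also leave the follow-up of discontinued patients to the full protocol. Further, the intention-to-treat statement concerns analysis by allocation, and the same section allows for missing data and a mixed-effects approach, so the analysis is weakened but not made impossible.

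The looser reading makes half of the Grade 4 sentence redundant and sits badly beside the Grade 3 wording. Nor is the point an omission: the article states a rule, and site staff would follow it. An analysis plan cannot recover outcomes that the protocol tells staff not to collect. A mixed model for a patient with baseline scores only has to predict from retained patients, so the shift goes away only as far as baseline explains the difference.

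The objections on size do stand in part. The article calls the trial low-risk and gives no Grade 4 rate, and k = 2 would mean 6.5% of an arm. The top value of D assumes no gain at all, although medical care and rehabilitation need not stop. The shift is computed for one arm without imputation; both arms receive conventional acupuncture, so losses in both could partly offset each other. It is also fair that the general withdrawal criteria may remove more patients than Grade 4 events will.

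**Conclusion.** The concern holds. As written, the Grade 4 rule takes a patient with a severe reaction out of the trial as well as off the needles, and the withdrawal criteria reinforce it. Up to six scheduled scores per patient are lost for a treatment-related reason, which undercuts the stated intention-to-treat analysis.

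The practical effect is probably small and may be nil. If one patient in an arm is lost, the arm mean shifts by 0.17 to 0.56 BI points, and if two are lost by 0.34 to 1.13, under the assumed D of 5.22 to 17.5 and an analysis of observed values only. The direction of any bias cannot be told from the article. The change is worth making because it costs little and avoids a treatment-related source of missing data.

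**What to change.** - **Patient safety, Grade 4:** replace termination of the trial for that patient with permanent discontinuation of study acupuncture. Add that these patients, if they agree, keep the Day 14 and 1-month assessments in Table 1 and remain in the intention-to-treat analysis, with the status of the event noted at those visits.
- **Withdrawal criteria:** state that stopping treatment because of an adverse reaction is treatment discontinuation, and does not trigger withdrawal from the study under the criterion on not receiving the assigned intervention.

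When needling must stop remains the sponsor's decision. The cost is wording in two places and continued contact with a few patients. The visits already exist, and the sample size stays at 62.
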